### Outcome measurements

In terms of short-term oncological outcomes, we expect the robot-assisted esophagectomy to be equivalent to the open approach for survival but accompanied by fewer complications [9-12]. The primary outcome of this study is therefore the percentage of overall complications (grade 2 and higher) as stated by the modified Clavien–Dindo classification (MCDC) of surgical complications [23].

Secondary biochemical outcomes include individual components of the primary endpoint (major complications; MCDC grades II to IV), including myocardial infarction, anastomotic leakage (clinical or radiologic diagnosis), anastomotic stenosis, chylothorax (chylous leakage, presence of chylous in chest tubes or indication to start low fat (2%)-containing tube feeding; Vivonex® T.E.N.; Nestlé, Lutry, Switzerland ), gastric tube necrosis (proven by gastroscopy), pulmonary embolus, deep vein thrombosis, vocal cord palsy or paralysis. Minor complications (MCDC grade I) will also be recorded. These include, for example, wound infections, pleural effusions and delayed gastric emptying.

Length of ICU–medium care unit stay (days), length of hospital stay (days), in hospital mortality and mortality within 30 and 60 days will be reported. For all patients, the cause of death will be noted. If applicable, the results of the autopsy report will be noted. Two-year, 3-year and 5-year disease-free survival and overall survival will be reported.

The operation time is defined as time from incision until closure (minutes) for both the thoracic phase and the abdominal phase of the procedure. For the robotic procedure, the set-up time will be recorded separately. Unexpected events and complications occurring during the operation will be recorded (for example, hemorrhage requiring transfusion, perforation of other organs) as well as blood loss during operation (milliliters per phase). In the case of conversion to thoracotomy or laparotomy, the reason for conversion has to be explained (absolute numbers/percentage).

The resected specimen will be marked by the surgical team for the position of lymph node dissection. Evaluation will be performed by an experienced pathologist using standard protocols. Stage grouping will take place according to the Union Internationale Contre le Cancer protocol using the Tumor, Node, Metastasis-7 classification [24]. Exact localization of the lymph nodes is an essential part of the pathologic examination [20]. The pathology report contains the following parameters: site of tumor, type and gradation, extension in the esophageal wall, margins of the resection, extent of resection (R0 (oncological radical resection), R1 or R2) [25], lymph node status with the number of lymph nodes, tumor regression grade (according to Mandard and colleagues) [26], vaso-invasion and perineural growth. Quality control of pathology will be provided by a specialized gastrointestinal pathologist ([name]).

The type and dose of used analgesics will be noted during the hospital admission period. A visual analogue scale for pain will be noted at the following times: preoperatively, the first 10 days after surgery and a fixed period during follow-up (6 weeks, 6 months and yearly postoperatively up to 5 years).

The quality-of-life questionnaires Short Form-36, EORTC Quality-of-life Questionnaire Core 30 (Dutch), EORTC OES18 (Dutch) and EQ-5D (Appendices 1 and 2) will be required at the following times: preoperatively <5 days, and 6 weeks, 6 months and yearly up to 5 years postoperatively.

The approach for the cost analysis is comparing actual direct medical costs incurred with both strategies up until 5 years after the operation. Costs estimates will be based on the recorded volumes and unit costs associated with both procedures. This includes the costs of operation rooms, costs of hospital and ICU stays, and costs associated with complications and reoperations.

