## Background

In 2008 an estimated 482,300 people were diagnosed with esophageal cancer, and 406,800 patients died of the disease worldwide [1]. Radical esophagolymphadenectomy is the cornerstone of the multimodality treatment with curative intent [2-5].

Transthoracic esophagectomy is the preferred surgical approach worldwide allowing for *en-bloc* resection of the tumor with the surrounding para-tracheal, subcarinal and para-esophageal lymph nodes [6,7]. However, the percentage of cardiopulmonary complications associated with the transthoracic approach is high (50 to 70%) [6].

Minimally invasive esophagectomy was designed to reduce surgical trauma, resulting in lower morbidity and mortality rates. With regard to minimally invasive esophagectomy, review of the literature shows a substantial decrease in blood loss, postoperative complications and days of hospital stay, with comparable oncologic results [8-12].

In 2003 the robot-assisted thoraco-laparoscopic approach was developed at the University Medical Center Utrecht (UMCU), the Netherlands [13]. Robot-assisted thoraco-laparoscopic esophagectomy facilitates complex minimally invasive procedures with an enlarged, three-dimensional field of view. The articulated instruments allow dissection with seven degrees of freedom [13,14].

Until now there have been no prospective randomized controlled trials comparing robot-assisted minimally invasive esophagectomy with conventional open transthoracic esophagectomy. We present the protocol of the first randomized controlled trial comparing these two surgical approaches.

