### Sample size calculation

Hypothesis: Compared with an open transthoracic esophagectomy, robot-assisted thoraco-laparoscopic esophagectomy will result in a lower percentage of overall complications (MCDC grade 2 and higher). In a prospective analysis of our own series, MCDC grade 2 to 5 complications were observed in 69% of all patients who underwent robot-assisted thoraco-laparoscopic esophagectomy and in 91% of all patients who underwent open transthoracic esophagectomy in our won series in the UMCU (2003 to 2010). We calculated that 102 patients (51 in each arm) with resectable esophageal cancer would be required to detect this 22% reduction in the absolute risk of overall complications (from 91% to 69% of patients) based on a two-sided significance level (alpha) of 0.05 and a power of 0.80. An estimated compensation of 10% for drop out is included in the total number of patients, resulting in a total of 112 patients, 56 in each arm. Figure 2 visualizes the final design.

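### The components of the primary endpoint stop at MCDC grade IV, while the endpoint and its planning rates run to grade 5, so a fatal complication is left out of its own component count

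*Protocol article*

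**What the plan says.** Three statements in the protocol article set the grade range.

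- **Primary endpoint** (Outcome measurements): "The primary outcome of this study is therefore the percentage of overall complications (grade 2 and higher". There is no upper limit.
- **Components** (next paragraph of the same section): "Secondary biochemical outcomes include individual components of the primary endpoint (major complications; MCDC grades II to IV". The list that follows names, among others, anastomotic leakage, gastric tube necrosis, myocardial infarction and pulmonary embolus. The paragraph then adds: "Minor complications (MCDC grade I) will also be recorded".
- **Planning rates** (Sample size calculation): "MCDC grade 2 to 5 complications were observed in 69% of all patients who underwent robot-assisted thoraco-laparoscopic esophagectomy". The figure given for open surgery, over the same grades, is 91%. The hypothesis in that section again uses grade 2 and higher.

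Outcome measurements also provides for in-hospital, 30-day and 60-day mortality, and for the cause of every death to be noted.

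**The concern.** A component of an endpoint should be a subset of that endpoint sorted by type of event, with the same severity threshold and no extra ceiling. Here a ceiling is added. An event that enters the component at grade II, III or IV leaves it when it reaches grade V, although it stays in the primary endpoint.

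The component count is then no longer monotone in severity. If leaks in one arm more often proved fatal, that arm's leak count would fall for this reason alone. The purpose of the component analysis is to show which complications drive any difference in the primary endpoint, and it would do so with the worst cases removed.

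**Working it through.** **1. Grade ranges side by side**

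| Item | Section | Grades covered | Grade V included? |
|---|---|---|---|
| Primary endpoint | Outcome measurements | 2 and higher | yes |
| Hypothesis | Sample size calculation | 2 and higher | yes |
| Planning rates 69% and 91% | Sample size calculation | 2 to 5 | yes |
| Components (major) | Outcome measurements | II to IV | no |
| Minor complications | Outcome measurements | I | no |

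The major and minor categories together cover grades I to IV. Grade V lies inside the endpoint and inside the rates used for planning, but in neither category.

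**2. Does the mismatch touch the sample size?** The inputs, all from Sample size calculation, are p1 = 0.91, p2 = 0.69, two-sided alpha 0.05 and power 0.80. Using the pooled two-proportion formula without continuity correction:

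n per arm = [1.96 × √(2 × p̄ × (1 − p̄)) + 0.8416 × √(p1(1 − p1) + p2(1 − p2))]² / (p1 − p2)²

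- p̄ = (0.91 + 0.69)/2 = 0.80, so √(2 × 0.80 × 0.20) = √0.32 = 0.5657.
- √(0.91 × 0.09 + 0.69 × 0.31) = √(0.0819 + 0.2139) = √0.2958 = 0.5439.
- Numerator: (1.96 × 0.5657 + 0.8416 × 0.5439)² = (1.1087 + 0.4577)² = 2.454.
- n = 2.454 / 0.22² = 2.454 / 0.0484 = 50.7, rounded up to 51 per arm and 102 in total.

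This matches the stated 51 and 102; power at 51 per arm is 80.2%. Adding 10% gives 102 × 1.10 = 112.2, stated as 112. These figures rest on grades 2 to 5 throughout, and the component range does not enter them. Extending the components to grade V leaves the endpoint, both rates and the sample size as they are.

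**3. How many events could be affected?** The article gives no rate of fatal complications. As an assumption only, if 2% to 5% of the 56 patients per arm died of a complication, that would be 56 × 0.02 = 1.1 to 56 × 0.05 = 2.8 patients per arm. These deaths would be spread over several components, and some would have causes that the article does not name. The loss from any single component would be smaller, and its direction between the arms is unknown.

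**The case against.** The best defence is that grades II to IV were meant as the non-fatal components, with death shown on its own. The separate mortality outcomes and the recorded causes of death make this plausible. One part of the defence stands: deaths are not lost from the trial, and a reader would see an excess in either arm. It does not settle the point, because the text presents these items as components of an endpoint that includes grade 5, states no restriction to non-fatal events, and does not say that grade V is tabulated by causal complication.

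A second objection is that components by diagnosis never sum to a rate per patient, since one patient can have several complications and the list is not exhaustive. That is correct. The complaint is therefore not that the table fails to add up, but that each component is truncated at its severe end.

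A reader might infer two further faults that the article does not support.

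- **Grading by diagnosis.** Of the minor complications the article says "These include, for example, wound infections, pleural effusions and delayed gastric emptying". This could be taken to assign those diagnoses to grade I whatever their severity. But grade I defines that category and the diagnoses only illustrate it. Nothing removes a wound infection of grade II from the primary endpoint.
- **Unnamed components.** The Background says that "the percentage of cardiopulmonary complications associated with the transthoracic approach is high (50 to 70" per cent, yet pneumonia and arrhythmia are not named. The list is open-ended, such events count in the primary endpoint when graded II or higher, and a full list is the kind of detail that a condensed article leaves to the full protocol.

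**Conclusion.** The inconsistency is real and stands in the current text: the components cover grades II to IV of an endpoint that covers grades II to V. Followed as written, a grade V complication counts in the primary endpoint and is missing from its own component.

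Its size is minor. Only the secondary component comparison is affected, and the primary analysis and sample size are untouched. A reader might infer that deaths disappear and that the arm with more deaths would look better overall. The separate reporting of mortality and cause of death rules that out; any distortion is limited to the component counts.

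One assumption is used. The article does not define grade V, and taking it to mean death follows the usual meaning of the scale. The mismatch in grade ranges holds without it.

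**What to change.** In Outcome measurements, replace the component range with *MCDC grade II and higher (II to V)*, and add that a fatal complication is counted under the complication that caused it as well as under mortality. If a restriction to non-fatal events was intended, the text must say so and state where grade V events are shown by cause.

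The cost is one phrase and one sentence. Cause of death is already to be noted for every patient, so no new data source is needed, and the primary endpoint, planning rates and sample size stay the same. The change is best made before the outcome data are analysed.

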### Sample size calculation

Hypothesis: Compared with an open transthoracic esophagectomy, robot-assisted thoraco-laparoscopic esophagectomy will result in a lower percentage of overall complications (MCDC grade 2 and higher). In a prospective analysis of our own series, MCDC grade 2 to 5 complications were observed in 69% of all patients who underwent robot-assisted thoraco-laparoscopic esophagectomy and in 91% of all patients who underwent open transthoracic esophagectomy in our won series in the UMCU (2003 to 2010). We calculated that 102 patients (51 in each arm) with resectable esophageal cancer would be required to detect this 22% reduction in the absolute risk of overall complications (from 91% to 69% of patients) based on a two-sided significance level (alpha) of 0.05 and a power of 0.80. An estimated compensation of 10% for drop out is included in the total number of patients, resulting in a total of 112 patients, 56 in each arm. Figure 2 visualizes the final design.

**Figure 2 F2:**
[figure not shown]
Flowchart for the ROBOT trial.

### Statistical analysis

All prospective data will be statistically analyzed using SPSS statistical software (SPSS Inc. Chicago, Illinois, USA. Data analysis will be performed in accordance with the intention-to-treat principle; additional per-protocol analysis will also be performed for tumor type, tumor stage and type of neoadjuvant treatment.

To evaluate significance of differences between the two groups, chi-squared and Fisher's exact tests will be used as appropriate for categorical variables, and the nonparametric Mann–Whitney U test for continuous variables.

To evaluate differences in disease-free and overall survival, Kaplan–Meier survival curves will be computed. Survival curves will be compared by log-rank test and multivariable analysis will be accomplished by the Cox regression model. The significance level will be set at 5%.

The approach for the cost analysis is comparing actual direct medical costs incurred with both strategies up until 5 years after the operation. Cost estimates will be based on the recorded volumes and unit costs associated with both procedures. This includes the costs of operation rooms, costs of hospital and ICU stays, and costs associated with complications and reoperations.

Pain scores will be analyzed using a linear mixed model using repeated-measures analysis. The quality-of-life questionnaires will be compared using covariance analysis (preoperative scores as covariables). The cost-effectiveness analysis will compare the mean costs and effects for both strategies and result in an incremental cost-effectiveness ratio. Uncertainty in the balance between costs and effects will be assessed with bootstrapping. A time horizon of 5 years will be applied, and costs and effects will be discounted according to Dutch guidelines.

If the baseline characteristics differ after randomization – that is, there is a lack of balance in the confounding factors – this will be corrected using multivariate analysis or using a net-benefit regression approach.

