### Aim of the study

This is a randomized controlled parallel-group, superiority trial of robot-assisted thoraco-laparoscopic esophagectomy versus open three-stage transthoracic esophagectomy in patients with resectable intrathoracic esophageal cancer.

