## Methods

### Objectives

Patients with resectable esophageal cancer are randomized at the outpatient department to either robot-assisted thoraco-laparoscopic esophagectomy or open three-stage transthoracic esophageal resection. The objective is to evaluate the efficacy, risks and cost-effectiveness of robot-assisted thoraco-laparoscopic esophagectomy as an alternative to open transthoracic esophagectomy as treatment for esophageal cancer. We hypothesize that robot-assisted minimally invasive thoraco-laparoscopic esophagectomy leads to a lower postoperative complication rate, less blood loss and a shorter hospital stay, with similar oncologic outcomes and better postoperative quality of life, compared with the open transthoracic esophagectomy (current reference standard of care).

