## Conclusion

This is the first randomized controlled trial designed to compare robot-assisted minimally invasive thoraco-laparoscopic esophagectomy with open transthoracic esophagectomy as surgical treatment for resectable esophageal cancer.

If our hypothesis is proven correct, robot-assisted minimally invasive thoraco-laparoscopic esophagectomy will result in a lower percentage of postoperative complications, lower blood loss and shorter hospital stay, but with at least similar oncologic outcomes and better postoperative quality of life compared with the open transthoracic esophagectomy (current standard).

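### Similar oncologic outcome is part of the stated hypothesis, but the named tests look only for a difference and the sample size rests on complications alone

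*Protocol article*

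**What the plan says.** The Aim of the study section declares a superiority design: "This is a randomized controlled parallel-group, superiority trial of robot-assisted thoraco-laparoscopic esophagectomy versus open three-stage transthoracic esophagectomy". The Objectives section lists five expectations for the robot-assisted operation: fewer complications, less blood loss, a shorter hospital stay, and then "with similar oncologic outcomes and better postoperative quality of life". The Discussion part of the Abstract and the Conclusion describe what follows if the hypothesis is proven correct. Both list the gains "but with at least similar oncologic outcomes and better postoperative quality of life".

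The Outcome measurements section gives the reason for choosing complications as the primary outcome: "we expect the robot-assisted esophagectomy to be equivalent to the open approach for survival but accompanied by fewer complications".

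For the oncologic outcomes, the Statistical analysis section gives the purpose as "To evaluate differences in disease-free and overall survival" and the method as "Survival curves will be compared by log-rank test and multivariable analysis will be accomplished by the Cox regression model". Other outcomes are tested for differences with chi-squared or Fisher's exact tests (categorical) and the Mann–Whitney test (continuous). The significance level is 5%.

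The Sample size calculation section uses complication rates only (91% open, 69% robot-assisted). It arrives at 102 patients, raised to 112 for drop-out. The article gives no event count, power, margin or interval criterion for any oncologic outcome.

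**The concern.** A log-rank test can reject equality of two survival curves. It cannot establish that they are close. In a small trial a non-significant result is likely even when survival is materially worse in one arm. If similarity is to be proven and only difference tests are named, the natural reading of a large p-value would be that similarity has been shown.

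The article presents the trial as the first randomized comparison of these operations, so a statement of oncologic similarity could influence adoption. The short-term report is planned after the last patient is discharged. Any such statement at that stage would rest on pathology (complete-resection rate and lymph node yield), where precision is also limited. The Discussion recognizes the general point elsewhere: it says that comparing robot-assisted with conventional minimally invasive surgery would need many patients because differences are probably small. The article does not apply that reasoning to survival here.

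**Working it through.** **The plan's own figure.** Inputs from Sample size calculation: 0.91 versus 0.69, two-sided alpha 0.05, power 0.80. With the pooled-variance formula and no continuity correction:

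n per arm = [1.96·√(2·0.80·0.20) + 0.8416·√(0.91·0.09 + 0.69·0.31)]² / 0.22² = (1.109 + 0.458)² / 0.0484 ≈ 50.7, so 51 per arm and 102 in total.

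Adding 10% gives 102 × 1.1 = 112.2, which matches the stated 112. The figure reproduces and contains no survival input.

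**Assumptions for survival.** The documents give no event rate. I take 40 to 80% of 112 patients with an event by 5 years, with 100% as a ceiling. D is the number of events, with 1:1 allocation and SE(log HR) = 2/√D.

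- 95% interval if the observed HR is 1.0: exp(±1.96 × 2/√D)
- Log-rank power against a true HR of 1.5: Φ(√D/2 × ln 1.5 − 1.96)
- Smallest margin that can be excluded with 80% power, true HR 1, one-sided 2.5%: exp[(1.96 + 0.8416) × 2/√D]

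| Patients with event | D | 95% interval at HR 1.0 | Power, true HR 1.5 | Non-significant, true HR 1.5 | Smallest margin |
|---|---|---|---|---|---|
| 40% | 45 | 0.56–1.80 | 27% | 73% | 2.31 |
| 60% | 67 | 0.62–1.61 | 38% | 62% | 1.98 |
| 80% | 90 | 0.66–1.51 | 48% | 52% | 1.81 |
| 100% (ceiling) | 112 | 0.69–1.45 | 57% | 43% | 1.70 |

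Example for 80%: 112 × 0.80 = 89.6 events, so √D/2 = 4.733. Then 4.733 × 0.4055 − 1.96 = −0.04, and Φ(−0.04) ≈ 0.48.

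With 102 patients in place of 112, power against HR 1.5 is 25 to 45% over the same 40 to 80% range.

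**Events needed to exclude a margin** (true HR 1, one-sided 2.5%, 80% power): D = 4 × (1.96 + 0.8416)² / (ln margin)² = 31.4 / (ln margin)².

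- Margin 1.25: 631 events
- Margin 1.50: 191 events
- Margin 1.75: 101 events
- Margin 2.0: 66 events

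No more than 112 events are possible. These margins are illustrations; the article states none.

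**Complete-resection rate.** The rate is not given. Assuming 90% in both arms, the 95% half-width for the difference is 1.96 × √(2 × 0.9 × 0.1/51) = 0.116 with 51 per arm, and 0.111 with 56 per arm. That is about 11 to 12 percentage points either way.

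**The case against.** The strongest reply is that the article never commits to the error. A reader might infer that the plan intends to declare equivalence from a non-significant test, but no sentence says so. In Outcome measurements, equivalence in survival is an expectation that explains the choice of primary outcome. Similar wording in the Discussion summarizes earlier literature. The Abstract and Conclusion are conditional on the hypothesis being proven. This stands, so the point cannot be put as a stated intention or as an existing decision rule.

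A reader might also infer that half of the hypothesis is at risk. The Objectives list five elements and oncologic similarity is one of them. The only powered hypothesis, in Sample size calculation, concerns complications. That correction stands too.

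Third, a margin or interval rule for a secondary outcome is often left to a full protocol or analysis plan, which is not shown. Log-rank with Cox is a conventional survival analysis, and Cox regression yields a hazard ratio and interval in any case. The absence of a margin would therefore not be a finding by itself. What remains is a mismatch between two things the article does print: a similarity claim that might be proven, and tests that cannot prove it.

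Finally, the magnitudes depend on assumed event rates, hazard ratios and margins. This is true of the exact figures but not of the direction. Even if every patient had an event, power against HR 1.5 would be 57%, and a margin below about 1.70 could not be excluded with 80% power.

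**Conclusion.** The mismatch is real and of moderate severity. The hypothesis and Conclusion treat similar or at least similar oncologic outcome as provable, while the tests named can only detect a difference and the sample size ignores survival.

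Under the assumed 40 to 80% event range, a 50% higher hazard would go undetected in roughly 52 to 73% of such trials. The data could exclude only hazard ratios of about 1.8 to 2.3 or more with 80% power. These figures assume 1:1 allocation, the usual normal approximation for the log hazard ratio and, for the margins, a true hazard ratio of 1.

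The oncologic outcomes are secondary. The primary comparison, its sample size of 112 and the interim efficacy rule, which concerns the primary endpoint, are unaffected.

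**What to change.** In Statistical analysis, commit to reporting the hazard ratios for overall and disease-free survival, and the differences in complete-resection rate and lymph node yield, each with a 95% interval. State that a non-significant test is not evidence of similarity.

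Then take one of two courses:

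- Label the oncologic comparison descriptive, and reword the Abstract, Objectives, Outcome measurements and Conclusion to match.
- Keep the word similar, but allow it only if the interval excludes a margin fixed before data are seen. The figures above show that only a wide survival margin is within reach.

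The first course fits the trial's size better. Either needs changes of wording only, with no extra patients or data. The price is a more modest permitted conclusion on oncologic outcome.

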### Study protocol

Patients are informed about the trial by one of our surgeons ([name] or [name]) at the outpatient department. After receiving the information, all patients have 1 week to consider their consent. After 1 week, patients are contacted by the coordinating researcher ([name]) to make an appointment to obtain and register informed consent.

After obtaining informed consent, randomization is done by computer-generated random numbers. Concealment of allocation is maintained by using sealed opaque envelopes. There is no blinding for the patient, surgeon and coordinating researcher because this is difficult in daily practice. However, the independent data monitoring safety committee is blinded to the allocated intervention. Within 1 week, patients will be informed about the allocated treatment. This study is completed funded by the Department of Surgery, UMCU. Multiple esophageal cancer biopsies for pathological analysis will be obtained through esophagogastroscopy, of which four biopsies will be snap frozen and stored for translational research. The physical status of the patient is assessed and preoperative testing is guided by institutional guidelines [17].

Neoadjuvant (radio)chemotherapy will be administered according to the current policy in the Netherlands and the UMCU [17]. Two additional blood samples will be obtained for translational research (proteomics) at the following times: before start of neoadjuvant treatment, the day of operation, after adjuvant treatment and with suspicion of recurrent disease.

After finishing preoperative neoadjuvant treatment, patients will be evaluated with a second computed tomography scan for metastases and resectability. When the tumor is considered to be resectable, patients will undergo the randomized intervention – either robot-assisted thoraco-laparoscopic esophagectomy or open three-stage transthoracic esophagectomy depending on randomization.

All resection specimens will be preserved and stored (biobank, tissue-microarray) for translational research.

The study started on 1 January 2012. Inclusion will take approximately 3 years. Follow-up for each patient will be 5 years. The total duration of the study will be 8 years.

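### Quality of life is measured at seven postoperative visits but fixed to covariance analysis, while pain at the same late visits gets a repeated-measures mixed model

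*Protocol article*

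**What the plan says.** The Objectives and Conclusion of the protocol article both include improved quality of life after robot-assisted surgery in the trial's hypothesis. Under Outcome measurements, four questionnaires (SF-36, QLQ-C30, OES18, EQ-5D) are due "preoperatively <5 days, and 6 weeks, 6 months and yearly up to 5 years postoperatively". Pain on a visual analogue scale is recorded before surgery, over the first ten days, and at "a fixed period during follow-up (6 weeks, 6 months and yearly postoperatively up to 5 years").

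The Statistical analysis section treats the two outcomes differently:

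- Pain: "Pain scores will be analyzed using a linear mixed model using repeated-measures analysis".
- Quality of life: "The quality-of-life questionnaires will be compared using covariance analysis (preoperative scores as covariables").

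The Study protocol section fixes when the covariate is measured relative to allocation. "After obtaining informed consent, randomization is done by computer-generated random numbers". Then "Within 1 week, patients will be informed about the allocated treatment", and "There is no blinding for the patient, surgeon and coordinating researcher because this is difficult in daily practice". Neoadjuvant treatment comes next, and "After finishing preoperative neoadjuvant treatment, patients will be evaluated with a second computed tomography scan for metastases and resectability". Only patients whose tumour is still judged resectable proceed to the allocated operation.

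**The concern.** Pain and quality of life are both patient-reported, repeated measures with the same long-term visits. Questionnaires will be missed over five years, and patients who miss them are unlikely to be a random subset. A mixed model keeps a patient who returned some postoperative forms and uses the earlier scores to inform the later ones. Conventional covariance analysis cannot. Done visit by visit, it ignores the other visits; done as repeated measures with listwise deletion, it discards anyone with a gap. What is at stake is the precision, and to some degree the unbiasedness, of a comparison that the article names in its hypothesis.

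A second, smaller issue concerns the covariate. It is a self-reported score given shortly before surgery by unblinded patients, after randomisation and, in the ordinary sequence, after they have been told their arm. A covariate that allocation could influence needs more caution than a true baseline.

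**Working it through.** **The plan's own figure.** The article gives no calculation for quality of life. Its only one is for complications, and it reproduces. With 91% against 69%, two-sided alpha 0.05, power 0.80 and mean proportion 0.80:

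n = [1.960·√(2·0.80·0.20) + 0.842·√(0.91·0.09 + 0.69·0.31)]² / 0.22² = (1.109 + 0.458)² / 0.0484 ≈ 50.7, so 51 per arm and 102 in total. Then 102 × 1.10 = 112.2, about 112, or 56 per arm. That is the most any quality-of-life comparison can use.

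**Visits.** 6 weeks and 6 months (2) plus years 1 to 5 (5) = 7 postoperative visits.

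**Side by side.**

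| | Pain | Quality of life |
|---|---|---|
| Visits from 6 weeks on | 7 | the same 7 |
| Stated method | repeated-measures linear mixed model | covariance analysis on preoperative score |
| Patient with some forms missing | contributes the visits available | conventionally excluded where a required form is missing |
| Patient who has died | no further scores | no further scores |

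**What fewer forms do to a single-visit comparison (assumed values).** The article gives no effect size, SD, correlation, survival or completion rate for quality of life. Assume a 0.5 SD effect and a correlation ρ = 0.5 between preoperative and postoperative scores. The residual SD is √(1 − ρ²) = 0.866, and power ≈ Φ[(0.5/0.866)·√(n/2) − 1.960].

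| Forms available | n per arm | Power |
|---|---|---|
| 100% | 56 | 86% |
| 80% | 44.8 | 78% |
| 60% | 33.6 | 66% |
| 40% | 22.4 | 49% |

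At 60% available, varying ρ from 0.3 to 0.7 moves power from 58% to 82%. These rows show the effect of having fewer patients at a visit for any reason. They are not the gain from changing method: the part due to death is lost under both.

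**What the choice of method does (assumed values).** One simulation used seven visits, a correlation of 0.6 between all scores and a true effect of 0.50 SD. Dropout depended on the previous score (missing at random), leaving 55% available at year 5. Complete-case covariance analysis at year 5 gave 0.47 SD on average; a likelihood-type estimate using all visits gave 0.50 SD. The attenuation is about 0.03 SD, or 6% of the effect.

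**The covariate (assumed values).** If knowing the arm shifted the preoperative score by d without altering the outcome, the adjusted difference would be off by about ρ × d. For d of 0.1 to 0.3 SD and ρ of 0.3 to 0.7, that is 0.3 × 0.1 = 0.03 SD up to 0.7 × 0.3 = 0.21 SD, in a direction that depends on the shift. Nothing in the article supports any particular d, including one different from zero.

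**The case against.** The best defence is that the sentence on quality of life is short and the article is condensed. It does not say that the analysis is done visit by visit, that only complete cases are used, or that missing scores are not imputed; an analysis plan may settle all of this. That stands, so loss of patients is the conventional consequence of the named method, not something the article states. What the article does fix is the method, and it fixes a different one for pain.

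Three further points also stand:

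- Adjusting for the score just before surgery is standard and usually efficient, and that score precedes the operation being compared. If expectation coloured scores both before and after surgery, adjustment might remove part of the distortion.
- A mixed model with the preoperative score as covariate still omits patients who lack that score. It does not by itself bring in patients found unresectable at restaging, since the schedule is anchored to the operation.
- The simulated attenuation is small.

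A reader might infer more than this, and the documents do not support it:

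- *That the covariate biases the result.* This needs allocation knowledge to have shifted the score. The article gives no evidence, size or direction.
- *That too few patients will remain at year 5 under this method.* No survival rate for the trial population is given, and deaths remove scores under either method.
- *That many unranked 5% tests will inflate false positives.* No testing scheme across scales and visits is stated, and ranking secondary comparisons is commonly left to an analysis plan.

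**Conclusion.** The point holds as a question of method for a secondary outcome. For repeated scores with gaps, the plan's own pain model is the better choice: it uses all available postoperative visits and rests on the weaker assumption about missed forms. The size of the benefit cannot be derived from the article. Under the assumptions shown it is modest in bias, and for precision it depends on how many forms are missed by living patients. The post-randomisation, unblinded timing of the preoperative score is a fact of the design and should be acknowledged, but no bias is demonstrated. The primary endpoint and the sample size are unaffected. This is a low-cost improvement, not a threat to the trial.

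**What to change.** In the Statistical analysis section, replace covariance analysis for the questionnaires with a linear mixed model of the kind already planned for pain: all seven postoperative visits as outcomes; arm, visit and arm-by-visit terms; the preoperative score as covariate. State that the result describes quality of life while alive. Make the change before quality-of-life scores are compared by arm.

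State as a limitation that the preoperative score is collected after randomisation by patients who know their arm. Add a sensitivity analysis without that covariate, which also admits patients who have postoperative forms but no preoperative one.

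The cost is some extra analysis work and reliance on a missing-at-random assumption for missed forms. No change to data collection is needed, so it applies equally to patients already enrolled.

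A questionnaire before randomisation is optional. It would be free of allocation knowledge, but it would precede neoadjuvant treatment, so it may predict postoperative scores less well, and it cannot be obtained for patients enrolled since January 2012. That would leave two baseline definitions within one trial.
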